### Participants

2.2

Eligible parents must (a) live in South Carolina, (b) be able to speak English or Spanish, (c) have access to a device to be able to attend Zoom video calls, and (d) must not have received any parent training services or health services aimed at improving their children's behaviors or lifestyle habits, such as sleep or physical activity promotion programs, in the 12 months before enrolling in the study. Parents must also be the primary caregivers of a child that (e) is between 3 and 6 years of age, (f) is Black/African American or Latiné/Hispanic, and (g) their child must not have any psychological or chronic health issues that significantly interfere with their communication (e.g., child does not understand basic instructions from their parent) or that limit their ability to engage in physical activity (e.g., child uses a wheelchair). Primary caregiver refers to a parent who resides in the same household as the child for at least 50% of the time and has primary custody of the child. We chose to include children with physical or mental health diagnoses as long as these issues did not interfere with key intervention targets, such as their ability to benefit from parenting strategies and adjust their lifestyle behaviors (e.g., physical activity level). These criteria were selected because they align with our universal prevention approach that targets families across the risk spectrum. Target recruitment for this study is 60 families (*n* = 30 experimental, *n* = 30 control).

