### Recruitment and Randomization

2.3

Participants will be recruited using a multifaceted strategy. This involves distributing flyers via email to community partners and displaying them at various locations like schools, daycares, churches, grocery stores, and health clinics. We will also participate in community events, such as back‐to‐school gatherings. To further assist with recruitment, we will hire three designated recruiters who are well‐connected in the community and have experience as community health workers. These recruiters will also act as interventionists (also referred to as parent coaches) for our study. Interested parents can express their interest by calling our designated study phone number, sending an email, or completing an online eligibility form by scanning the QR code shown on the study flyer. After that, research assistants from the ROOTS team will confirm their eligibility during a screening call. Informed consent will be gathered through this screening call and by reviewing qualtrics online forms. Black and Latiné participants will be randomized separately to ensure adequate representation of each ethnic‐racial group within each treatment condition (participants of AfroLatiné descent will be randomized based on language preference). To create each randomization scheme, we will use Excel's random number generator function to produce and save 30 random numbers. These assignments will be hidden in Excel to prevent access by research staff making screening calls. After consenting to participate and completing the T1 assessment, participants will receive a study ID number. This ID number will be added to the appropriate randomization scheme (either Black or Latiné) in the order of enrollment. The random assignment will then be revealed by a designated study staff member.

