#### Demographics and Other Covariates

2.5.4

We will collect various demographic measures (at T1) and relevant covariates that have been shown to impact key study outcomes (T1–T3). Demographic measures will include characteristics such as parent and child gender, race/ethnicity, preferred language, years lived in the United States, age, and socioeconomic factors. Other covariates will include measures of parents' perceived discrimination (everyday discrimination scale; Williams et al. 1997), ethnic/racial identity (multidimensional inventory of black identity; Sellers et al. 1998), and childhood adversity exposure (expanded ACEs; Cronholm et al. 2015). These demographic and sociocultural factors have been consistently shown to be associated with parenting and child health (e.g., parent ACEs with harsh parenting; Wattanatchariya et al. 2024; parental discrimination and ethnic identity with ethnic‐racial socialization practices; White‐Johnson et al. 2010; socioeconomic status with child physical activity and behavioral problems; Gautam et al. 2023), and will therefore be examined as potential covariates or moderators in our analyses.

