### Data Analysis Plan

2.8

To evaluate the feasibility of the ROOTS program (Aim 1), we will use a combination of descriptive statistics and qualitative methods. Descriptive analyses will report progression criteria, including recruitment, enrollment, attendance, and completion rates. We will also compute means, standard deviations, and response distributions on quantitative implementation measures, such as the acceptability of intervention measure (AIM), feasibility of intervention measure (FIM), and intervention appropriateness measure (IAM). To further assess implementation outcomes, we will analyze qualitative interviews from parents and interventionists using thematic analysis (e.g., Braun and Clarke 2006). These interviews will be independently coded by multiple members of the study team using the CFIR framework to identify salient barriers and facilitators across domains (e.g., intervention characteristics, inner and outer settings). We will also map emergent findings onto RE‐AIM dimensions (e.g., adoption, implementation, and maintenance) to assess feasibility and inform potential for scale‐up. Following independent coding, the team will engage in a structured consensus process to resolve discrepancies and refine themes. Final themes will be retained only if they (a) appear across multiple interviews and (b) are independently identified by all coders and agreed upon through consensus discussion.

Preliminary tests of ROOTS' effects (i.e., Aim 2) will be conducted using multilevel modeling (MLM; Fitzmaurice et al. 2011) to account for repeated measures nested within participants in R (R Core Team 2024). Separate mixed effects models will be estimated for each outcome: child social‐emotional functioning, child sleep, physical activity, and sedentary behavior, and parenting variables. Each model will include fixed effects for time (T1, T2, and T3), group (ROOTS vs. control), and the time × group interaction, with child age, gender, and various socioeconomic factors as covariates. All models will follow an intent‐to‐treat (ITT) design, including all randomized participants regardless of intervention completion (Hollis and Campbell 1999). Because this is a pilot study, emphasis will be placed on estimating effect sizes and 95% confidence intervals rather than formal hypothesis testing, consistent with best practices for early‐phase research (Thabane et al. 2010).

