Accelerometer data will be downloaded and processed using the GGIR package in R (Van Hees et al. 2015). For sleep, we will use the L512 algorithm to estimate the primary sleep period and extract average nightly sleep duration and quality (e.g., wake after sleep onset). For physical activity, we will calculate daily time spent in sedentary, light, and moderate‐to‐vigorous intensity categories using preschool‐specific cut‐points validated for axivity devices (Migueles et al. 2019; Roscoe et al. 2017). Values will be averaged across all valid days at each timepoint. Finally, for descriptive purposes, we will conduct subgroup analyses based on delivery language (English vs. Spanish) and participant ethnic‐racial background (Latiné vs. non‐Latiné Black) by comparing the effect sizes of intervention outcomes across these groups. We will use restricted maximum likelihood (REML) estimation to analyze longitudinal outcomes, as REML provides less biased estimates of variance components than traditional maximum likelihood, particularly in models with small to moderate sample sizes and repeated measures. REML is well‐suited for linear mixed‐effects models because it accounts for the loss of degrees of freedom associated with estimating fixed effects, which improves the estimation of random effects and yields more reliable standard errors (McNeish 2017).

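### The descriptive subgroup comparison has no planned estimate or interval for the difference between subgroup effects, and with about 15 families per arm in each ethnic-racial group that interval would be roughly ±0.8 to ±1.0 SD

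*Protocol article*

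**What the plan says.** In the Data Analysis Plan (section 2.8), the Aim 2 model is specified for each outcome: "Each model will include fixed effects for time (T1, T2, and T3), group (ROOTS vs. control), and the time × group interaction". Adjustment is for socioeconomic factors and for the child's gender and age. The same section states that "emphasis will be placed on estimating effect sizes and 95% confidence intervals rather than formal hypothesis testing".

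It then says that "for descriptive purposes, we will conduct subgroup analyses based on delivery language (English vs. Spanish" and by ethnic-racial background (Latiné vs. non-Latiné Black). The stated method is "by comparing the effect sizes of intervention outcomes across these groups".

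Demographics and Other Covariates (section 2.5.4) lists race/ethnicity and preferred language among the measures collected. It says that the demographic and sociocultural factors "will therefore be examined as potential covariates or moderators in our analyses".

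On numbers, Participants (section 2.2) says "Target recruitment for this study is 60 families", 30 per arm. Recruitment and Randomization (section 2.3) says that "Black and Latiné participants will be randomized separately" and that each scheme is made by using a random number generator "to produce and save 30 random numbers". The English/Spanish split is not given.

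**The concern.** A subgroup analysis asks whether the effect differs between groups, so the quantity of interest is the difference between two effects. The plan names a comparison of effect sizes, and the only model it specifies has no subgroup term. Nothing described produces that difference with a measure of its uncertainty. Intervals around each subgroup effect do not supply it: the standard error of the difference is larger than that of either effect, and whether two intervals overlap is a poor guide to it.

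With cells this small, sizeable gaps arise by chance when the true effects are equal. Without the interval, a reader of the results cannot tell such a gap from a real one. What is at stake is the interpretability of a secondary, descriptive result, not the main estimates.

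**Working it through.** The article gives no SD, effect size or precision figure, so there is no stated number to reproduce. The calculation uses a normal approximation in SD units, with equal variances.

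**Inputs from the protocol article**
- 60 families, 1:1 (sections 2.1 and 2.2).
- Two schemes of 30 (section 2.3), so 60 / 2 / 2 = 15 families per arm within each ethnic-racial group. No blocking is described, so 15:15 is expected but not guaranteed.
- 60% completing all three assessments, the lower edge of the "go" criterion (section 2.5.1), used only as a sensitivity value.

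**Assumptions (not in the article)**
- Correlation ρ between T1 and later scores: 0.6 as the working value.
- Language split: 30/30 to 50/10.

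**Unadjusted, full retention**
- SE of one subgroup effect = √(2/15) = 0.365.
- SE of the difference between two subgroup effects = √(4/15) = 0.516.
- With no true difference, median absolute gap = 0.674 × 0.516 = 0.35 SD; mean = √(2/π) × 0.516 = 0.41 SD.
- Probability of a gap above 0.4 SD = 0.44; above 0.5 SD = 0.33.
- 95% half-width = 1.96 × 0.516 = ±1.01 SD.
- Simulating unblocked allocation within strata of 30 gives mean 0.42, median 0.35 and 95th percentile 1.03, so possible imbalance changes little.

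**Using T1, ρ = 0.6, full retention**
- T1 as a covariate: 0.516 × √(1 − 0.36) = 0.413; half-width ±0.81 SD; mean chance gap 0.33 SD.
- T1 as a repeated outcome, as in the planned model, with an unconstrained change contrast: 0.516 × √(2 × 0.4) = 0.462; half-width 1.96 × 0.462 = ±0.91 SD; mean chance gap 0.798 × 0.462 = 0.37 SD.

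**Sensitivity**
- 60% retention (9 per cell), unadjusted: SE = √(4/9) = 0.667; half-width ±1.31 SD. With T1 as a covariate at ρ = 0.6: ±1.05 SD. This is pessimistic for a mixed model, which also uses partly observed families.
- Language split 45/15, unadjusted: SE = √(2/22.5 + 2/7.5) = 0.596; half-width ±1.17 SD.
- Language split 50/10, unadjusted: SE = √(2/25 + 2/5) = 0.693; half-width ±1.36 SD.
- A higher correlation helps: at ρ = 0.8 with T1 as a covariate and full retention, half-width ±0.61 SD and mean chance gap 0.25 SD.

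**Size of the fuller model.** With three categorical timepoints, adding a two-level subgroup factor in full requires subgroup (1), group × subgroup (1), time × subgroup (2) and group × time × subgroup (2): six fixed-effect parameters.

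**The case against.** The strongest reply is that this is a condensed article. It does not say that intervals will be left out of the subgroup comparison. It puts general emphasis on effect sizes with 95% confidence intervals, and section 2.5.4 foresees moderator analyses for a set of factors that includes race/ethnicity and language. Moderation is ordinarily estimated through an interaction, so the full plan may already contain the remedy. The analysis is also labelled descriptive.

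Part of this stands. The label limits the harm, and a fuller document may settle the matter. But the article does state a method for the subgroups. The model it specifies has no subgroup term, the general emphasis on intervals is not tied to the difference between subgroup effects, and being examined as a potential covariate or moderator is not a commitment to an interaction estimate.

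A reader might infer three stronger things that the document does not support:
- **That the comparison will be made by eye, or with each effect scaled by its own subgroup SD.** Neither is stated.
- **That a decision to tailor the programme to one group, or to proceed to a larger trial, will rest on this comparison.** Section 2.4.2 bases tailoring on existing evidence. The progression criteria in section 2.5.1 concern recruitment, enrollment, session completion and assessment completion, reviewed with data such as fidelity and satisfaction.
- **That any difference whose interval includes zero should be barred from the report.** That would be a significance test, at odds with the plan's preference for estimation.

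**Conclusion.** The point holds in a limited form. The article describes a comparison of subgroup effect sizes and provides no estimate with an interval for their difference. For ethnic-racial background, with about 15 families per arm in each group and full retention, a chance gap of 0.35 to 0.41 SD is typical without adjustment. The 95% half-width is about ±1.0 SD unadjusted and about ±0.8 to ±0.9 SD at an assumed T1 correlation of 0.6, depending on whether T1 is a covariate or a repeated outcome.

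The typical gap is not the limit of chance, and all these figures move with the assumed correlation and with retention. Fifteen per cell follows only for ethnic-racial background. For language an equal split is the most favourable case, and any uneven split widens the interval. Because the analysis is descriptive and no decision is tied to it, this is a worthwhile improvement in reporting, not a threat to the trial's main aims.

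**What to change.** Replace the comparison of separate effect sizes in section 2.8 with the following. For each outcome and each subgroup factor, fit one model to all families containing group × time × subgroup and its lower-order terms. Report the difference between the subgroup effects at T2 and at T3 with its 95% confidence interval, on a common pooled T1 SD. Describe the result as exploratory and state the width of the interval. The same form would suit any categorical factor examined as a moderator under section 2.5.4.

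No extra data are needed. The cost is a short change of wording, six more fixed-effect parameters per two-level factor in a 60-family pilot, and intervals that will be visibly wide. That width is itself the information a reader needs.

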### Dissemination Plans

2.9

The results of this study will be disseminated through various mediums and communicated to participants, community organizations, and the scholarly community. Proposed topics for presentation or publication will be shared with the PI, research lab, and the coordinating research center. For example, we will create infographics summarizing study results to send to participants and community organizations and post on social media. We plan to submit our findings to academic conferences and journal outlets. Data will be available on the Qualitative Data Repository, and study materials and full assessment protocols will be shared upon reasonable request to the first author. Statistical code used for the proposed analysis will be shared alongside the published findings.

## Discussion

3

This study will provide needed information regarding whether ethnic‐racial socialization and healthy lifestyle behaviors can be integrated into a brief parenting intervention to enhance the health of Black and Latiné children. Specifically, the study will examine the acceptability, feasibility, and preliminary effects of the ROOTS program by tracking changes in longitudinal child and parent outcomes and gathering information about various implementation outcomes shown to influence intervention delivery, such as fidelity, acceptability, reach, and perceived barriers and facilitators. This proposal's integration of ethnic‐racial socialization—a key factor in buffering the negative effects of racism for minoritized groups—into a preventive parenting intervention represents one of the first efforts of its kind. This addition has the potential to enhance intervention engagement and bolster child health outcomes by mitigating the effects of racism on child health (Coard et al. 2021). For example, one study used data from two randomized clinical trials of a parenting intervention that incorporated ethnic‐racial socialization and found that the intervention buffered the effects of prior discrimination on various child outcomes (Brody et al. 2021).

Many family‐based health promotion interventions have focused on the emotional and physical health domains separately, rather than in the same intervention. A low‐dose, early, preventive intervention offers a solution to several of the limitations of past family‐based interventions. Because parenting practices can be used to promote a wide range of child health behaviors, an integrated parent training intervention has the potential to impact children's physical and emotional health while minimizing the added burden on parents and providers.

One potential concern is that the dose of the parenting intervention would be insufficient to produce the expected changes in certain target outcomes (i.e., ethnic‐racial socialization and healthy lifestyle behaviors). This is particularly relevant for the healthy lifestyle content, as other interventions for this domain are often more intensive. However, this concern might be tempered by the inclusion of well‐established determinants of child health outcomes (e.g., positive parenting, ethnic‐racial socialization), which could have synergistic effects on study outcomes, thereby bolstering program effects. The proposed intervention also differs from past family‐based interventions, in that it is focused on universal prevention and, therefore, requires a less intensive intervention as compared to other prevention approaches (e.g., indicated prevention) that solely target individuals experiencing higher levels of risk.

### Implications and Conclusion

3.1

This intervention protocol can serve as a valuable resource for program evaluators, intervention developers, and clinical researchers interested in implementing culturally responsive strategies for family‐based health promotion. We provided important behind‐the‐scenes details about the processes and decisions often involved in complex intervention development, which are frequently left out of existing literature. For example, numerous scholars have highlighted the lack of transparency in intervention development, calling it the “Cinderella” black box (Murray et al. 2023). This makes it challenging for interested parties to learn from or replicate intervention development strategies. Importantly, our protocol outlined the various steps taken to develop the ROOTS program, guided by an intervention mapping approach, such as identifying key determinants of child health and selecting evidence‐based strategies. We also considered the unique needs of Black and Latiné families and selected positive parenting and ethnic‐racial socialization strategies that could be tailored to both groups. Such structured, culturally attuned approaches to intervention development can help improve the quality and reach of family‐based interventions for minoritized populations. Overall, the expected contribution of our project is to provide important foundational knowledge regarding the feasibility of combining ethnic‐racial socialization and healthy lifestyle behaviors into a brief parenting intervention to enhance minoritized children's physical and emotional health. If successful, the results of this pilot trial could lead to advancements in prevention efforts focused on improving child health‐related outcomes, and ultimately lead to decreased health inequities for minoritized children.

## Ethics Statement

The study protocol was approved by the University of South Carolina's Institutional Review Board (IRB Protocol #Pro00124236) and aligns with the SPIRIT reporting guidelines (Chan et al. 2013). All participants will provide consent to participate in the study. Consent for publication will not be required because no identifying information will be included.

## Data Availability

Data will be made available in an online repository and other materials can be shared upon reasonable request.
